# Effect of vitamin D supplementation on brain waves, behavioral performance, nitric oxide, malondialdehyde, and high-sensitivity C-reactive protein in children with attention deficit/hyperactivity disorder: study protocol for a randomized clinical trial

**DOI:** 10.1186/s13063-022-06837-1

**Published:** 2022-10-22

**Keywords:** Attention deficit/hyperactivity disorder, Vitamin D, Brain waves, Behavioral performance, Oxidative stress

## Abstract

**Background:**

Attention deficit/hyperactivity disorder (ADHD) is the most common chronic mental and behavioral disorder among children. Some studies showed the lower levels of vitamin D in patients with ADHD compared with the healthy people. Few clinical trials were conducted in this field. The present study will be performed to examine the effect of vitamin D supplementation in children with ADHD.

**Methods:**

We will conduct a double-blind, randomized controlled clinical trial to investigate the effect of vitamin D supplementation on brain waves, behavioral performance, serum nitric oxide, malondialdehyde, and high-sensitivity C-reactive protein in 50 patients with ADHD. The intervention group will receive one capsule 50,000 IU vitamin D every week, for 8 weeks. The control group will receive one placebo capsule containing 1000 mg olive oil every week. Electroencephalography will be performed for 10 min using Brain Master Discovery from 19 scalp sites both before the first intervention and the 10 sessions of the therapy. The artifact-free periods of 1-min electroencephalography data will be analyzed for quantitative electroencephalography measures.

**Discussion:**

For the first time, this clinical trial will evaluate the effect of vitamin D supplementation on brain waves, serum nitric oxide, malondialdehyde, and high-sensitivity C-reactive protein in patients with ADHD. The results of the present clinical trial will provide a better vision about the vitamin D efficacy in patients with ADHD.

**Trial registration:**

Registered on 5 November 2020 at Iranian Registry of Clinical Trials with code number IRCT20200922048802N1 (https://www.irct.ir/trial/51410).

## Background

Attention deficit/hyperactivity disorder (ADHD) is one of the most common neurocognitive behavioral disorders in children [1]. The main symptoms of ADHD are hyperactivity, impulsivity, and inattention, and it is also associated with psychiatric disorders such as autism, anxiety, and oppositional defiant disorder (ODD) [2, 3]. The global prevalence of ADHD is 6–7% [4]. Neurotransmitters dopamine and serotonin have a critical role in attention, concentration, and other cognitive functions [5]. Evidence revealed disorders in the dopaminergic system of basal ganglia in ADHD children [5, 6]. In addition, ADHD is accompanied with spectral changes in subject brain waves including the higher rate of delta and theta values power spectra as well as the theta/beta and theta/alpha ratios of the frontal and central areas and the reduced power of sensorimotor rhythm (SMR) in the central and motor cortices [7, 8]. Although the pathophysiology is not fully clear, oxidative stress and inflammation are linked to ADHD [9, 10]. Levels of malondialdehyde (MDA), which is a marker of oxidative stress, is high among patients with ADHD [11]. In addition, patients with ADHD have lower levels of antioxidant enzymes [12, 13]. It has been suggested that nitric oxide (NO), which is an important antioxidant molecule for the proper function of the central nervous system, has a functional role in learning and memory [14–16]. On the other hand, cytokines have a critical role in the metabolism of tryptophan and dopaminergic pathways in the brain [10, 17]. Patients with ADHD have higher levels of pro-inflammatory markers and lower levels of the anti-inflammatory cytokine interleukin 4 (IL-4) in the cerebrospinal fluid [18]. Likewise, higher serum level of inflammatory markers is associated with higher ADHD symptom severity [19]. It has been reported that elevated levels of C-reactive protein (CRP), which is a main marker of inflammation in clinical practice, is associated with impairments in memory, learning ability, and mental flexibility [20, 21].

Central nervous system (CNS) stimulants like methylphenidate and amphetamine are prescribed for patients with ADHD [22]. However, CNS stimulants have various side effects such as arrhythmia, insomnia, irritability, and decreased appetite, and the rate of compliance to this treatment is not high [23–25]. In addition, atomoxetine and alpha-2-agonists (like clonidine and guanfacine), which are non-stimulant drugs for ADHD, have several side effects including decreased appetite, vomiting, nausea, diarrhea, dry mouth, somnolence, fatigue, mood swings, dizziness, and constipation [23, 26]. Moreover, 30% of children with ADHD do not respond to drug treatments [22, 27]. The recent evidence suggested the beneficial effects of vitamin D on neurocognitive behavioral disorders [28, 29]. Vitamin D is a fat-soluble vitamin as well as a steroid hormone and acts in various organs of the body by binding to the vitamin D receptor (VDR) [30–32]. High levels of the VDR as well as 1*α*-hydroxylase enzyme (activator of vitamin D) in the brain suggest that vitamin D probably has physiological functions in the brain [33]. Serotonin, which is synthesized in the brain, is regulated by vitamin D [34]. Furthermore, vitamin D increases the expression of tyrosine kinase as an enzyme involved in the dopamine synthesis [35]. In addition, vitamin D has fewer side effects compared to other treatments for ADHD [23, 36]. Therefore, the compliance rate to treatment with vitamin D can be higher than treatment with common drugs for ADHD. Vitamin D can improve oxidative stress and inflammation via reducing the production of inflammatory markers such as interleukin-6 (IL-6), and tumor necrosis factor-α (TNF-α), inhibiting the proliferation of pro-inflammatory cells, increasing the expression of antioxidants and anti-inflammatory cytokines, attenuating endoplasmic reticulum stress, and decreasing mitochondrial dysfunctions [37–40].

A study found that higher level of vitamin D in pregnant women reduces risk of ADHD-like symptoms in the offspring [41]. Furthermore, some studies showed the lower levels of vitamin D in patients with ADHD compared with the healthy controls [6, 42, 43]. A meta-analysis of observational studies confirmed lower levels of vitamin D in patients with ADHD [44]. Two clinical trials evaluated the effect of vitamin D supplementation on the behavioral performance of children with ADHD and showed inconsistent results [45, 46]. Moreover, there is no clinical trial evaluating the effect of vitamin D on brain waves, oxidative stress and inflammation in patients with ADHD. The present study was designed to examine the effect of vitamin D supplementation on brain waves, behavioral performance, serum NO, MDA, and high sensitivity CRP (hs-CRP) in children with ADHD.

## Methods

### Study design

This study will be performed as a randomized double-blind placebo-controlled clinical trial (RCT) to investigate the effect of vitamin D supplementation for 8 weeks on brain waves, behavioral performance, NO, MDA, and hs-CRP in children with ADHD. The primary outcomes of the present study are the status of brain waves and the severity of ADHD symptoms. We will also evaluate serum NO, MDA, and hs-CRP as secondary outcomes. The present study protocol is derived from two studies that designed as the student theses with titles: [1] the effect of vitamin D supplementation on the brain mapping and behavioral performance of children with ADHD: a double-blind randomized controlled trial and [2] the effect of vitamin D supplementation on serum levels of MDA, NO, and hs-CRP in children with ADHD. The flow chart of study protocol is presented in Fig. 1.

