### Objectives

Primary objectives are as follows:Compare the status of brain waves between the 2 groups and within each group, before and after intervention.Compare the mean ADHD symptoms severity between the 2 groups and within each group, before and after intervention.

In addition, the following objectives are the secondary objectives of the study:Compare the mean serum hs-CRP between the 2 groups and within each group, before and after intervention.Compare the mean of serum MDA, between the 2 groups and within each group, before and after intervention.Compare the mean of serum NO, between the 2 groups and within each group, before and after intervention.

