### Sample size

Sample size is calculated based on means and standard deviations for Conners’ ADHD Index, as the primary outcome of the study of Gow et al. [49] by considering 95% confidence interval, 80% power (*α* = 0.05 and *β* = 0.2), and using the following formula:$$n=\frac{{\left(\textrm{z}\frac{\alpha }{2}+\textrm{z}\upbeta \right)}^2\times 2{S}^2\ }{{\left(x1-x2\right)}^2}$$

Considering a drop-out rate of approximately 10%, the final sample size needed was estimated to be 25 per group. All participants will be included in the RCT if they meet the inclusion criteria and are willing to participate in the study, until the estimated sample size is completed.

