### Data collection

#### ADHD symptoms assessment

In the assessment of ADHD symptoms, Conners’ behavior rating scale which is a clinical tool evaluating child behavioral disorders will be used. Conners’ rating scale is divided into three categories, which are determined by the person who filled it (parent, teacher and self-report). For this trial, Conners’ parent rating scale (CPRS) [51] will be used. CPRS checklist makes parental reports of the children’s basic problems in the setting of outpatient psychiatry. The CPRS includes questions about different aspect of patients’ problems and shows different type of ADHD symptoms [51]. Conners’ questions gives ADHD Conners scores that indicates the severity of ADHD symptoms. In addition, all questions can be divided into three subscales by symptoms including inattention, hyperactivity/impulsivity, and combination type.

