#### Electroencephalography

Electroencephalography (EEG) will be performed for 10 min using Brain Master Discovery from 19 scalp sites both before the first intervention and the 10 sessions of the therapy. The artifact-free periods of 1-min EEG data will be analyzed for quantitative EEG (QEEG) measures using the Neuroguide software. Background rhythm in relative power of theta (4–7.5 Hz), alpha (8–12 Hz) of the frontal and central electrodes, and the theta/beta and theta/alpha ratios in motor cortices will be analyzed by the SPSS software version 24.

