#### Statistical analysis

SPSS version 24 (SPSS, Inc.) will be used for data analysis. The analyses will be performed using the intention-to-treat (ITT) approaches. Using Kolmogorov-Smirnov test, normal distribution of variables will be assessed. Comparing the qualitative variables between two groups will be performed using chi-squared test. To compare the means of normal variables at baseline, at the end of study, and compare the mean changes of normal data between two groups, independent *t*-test will be used. To compare normal variables within the groups, paired sample *t*-test will be applied. Using Mann-Whitney *U* test, comparing abnormal data between the two groups at baseline and after the intervention as well as comparing the mean changes of abnormal data between two groups will be performed. Wilcoxon test will be used to compare the abnormal data within the groups. To control covariates, ANCOVA will be carried out. *P* < 0.05 will be considered significant.

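### Two unranked primary outcomes, one a family of at least four EEG measures, are tested at an unadjusted 0.05, and the 80% power covers only the Conners' ADHD Index

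*Protocol article*

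**What the plan says.** All references are to the protocol article.

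- **Study design:** "The primary outcomes of the present study are the status of brain waves and the severity of ADHD symptoms". Serum markers are secondary.
- **Objectives:** both outcomes return as primary objectives, with between-group and within-group comparisons in each: "Compare the status of brain waves between the 2 groups and within each group, before and after intervention" and "Compare the mean ADHD symptoms severity between the 2 groups and within each group, before and after intervention". Neither is put first for decision purposes.
- **Electroencephalography:** the measures to be analysed are "Background rhythm in relative power of theta (4–7.5 Hz), alpha (8–12 Hz) of the frontal and central electrodes", followed by two ratios, theta/beta and theta/alpha, in motor cortices.
- **ADHD symptoms assessment:** the Conners score is said to indicate symptom severity. The text adds that "all questions can be divided into three subscales by symptoms including inattention, hyperactivity/impulsivity, and combination type", but does not call the subscales primary.
- **Sample size:** "Sample size is calculated based on means and standard deviations for Conners’ ADHD Index", at alpha 0.05 and 80% power, giving 25 per group after about 10% dropout.
- **Statistical analysis:** for P, below "0.05 will be considered significant". No alpha split, testing order, adjustment or requirement that both primaries succeed is stated.

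**The concern.** A 5% error rate for the trial's main claim needs either one deciding test or a rule that links several. The article fixes two primaries and a flat threshold and gives no such rule. One of the two is not a single variable, so in practice a claim of success could rest on whichever EEG measure, or the Conners' score, falls below 0.05. In a trial of 50 children, a significant result on one of several EEG measures could then be reported as a positive primary outcome.

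The second issue is separate. The trial is sized on one Conners' score. Brain waves are listed first among the primaries, yet no EEG effect size, variance or power is given. A null EEG result would be hard to interpret, and the 80% figure could be read as covering both outcomes when it does not. This is a power gap and does not itself raise the false-positive rate.

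**Working it through.** **1. The plan's own figure.** The stated formula, with S as the SD and d = (x1 − x2)/S, is n = 2(1.96 + 0.8416)²/d² = 15.70/d² per group. The means and SDs are not printed, so 25 cannot be rebuilt forwards. Working backwards with 10% dropout:

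- 21/0.9 = 23.3, rounds up to 24
- 22/0.9 = 24.4, rounds up to 25
- 23/0.9 = 25.6, rounds up to 26

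So 22 evaluable per group is the whole number that leads to 25. The implied standardized difference is √(15.70/22) = 0.845, or √(15.70/22.5) = 0.835 if 25 × 0.9 = 22.5 is left unrounded. Both are inferred and concern the Conners' ADHD Index only.

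**2. How many primary tests the text supports.**

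- Two: one EEG measure and one Conners' score. This is the floor.
- Five: theta power, alpha power, theta/beta, theta/alpha and one Conners' score.
- Seven: theta and alpha power each split into frontal and central (4), two ratios and one Conners' score.

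Subscales, baseline comparisons, within-group tests and the choice between end value and change are not counted.

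**3. Chance of at least one false positive, each test at two-sided 0.05.** If the tests are independent, this is 1 − 0.95^k:

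- k = 2: 1 − 0.9025 = 9.75%
- k = 5: 1 − 0.7738 = 22.6%
- k = 7: 1 − 0.6983 = 30.2%

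With equal correlation ρ between test statistics, it is 1 − ∫ φ(u)[Φ((1.96 − √ρ·u)/√(1−ρ)) − Φ((−1.96 − √ρ·u)/√(1−ρ))]^k du. The correlations are assumptions, because the article gives none.

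| Tests | ρ = 0 | 0.5 | 0.7 | 0.9 |
|---|---|---|---|---|
| 2 | 9.8% | 9.1% | 8.4% | 7.0% |
| 5 | 22.6% | 18.3% | 14.8% | 10.2% |
| 7 | 30.2% | 23.0% | 17.8% | 11.4% |

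A different pattern, with EEG measures correlated among themselves at 0.5, 0.7 or 0.9 and Conners' independent of them, gives 19.8%, 17.4% and 13.9% for five tests. These lie inside the same range.

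**4. If both primaries had to succeed.** The type I error would stay at or below 5%. Joint power would fall instead: with 80% on each and independence, 0.80 × 0.80 = 64%. The article states no such requirement.

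**5. Conners' power if alpha were split over two primaries (0.025 each), 22 evaluable per arm.**

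| Method | d | Power at 0.05 | Power at 0.025 |
|---|---|---|---|
| t-test | 0.835 | 77% | 67% |
| Normal approximation | 0.845 | 80% | 71% |

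The loss is about 9 to 10 points when each method is compared with itself. It arises only under an adjustment that the plan does not make.

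**The case against.** The strongest reply is that this is an article, and multiplicity handling is commonly left to an analysis plan that is not shown. That covers details of the EEG contrast. It does not cover what the article itself fixes: two unranked primaries, one of them a family, a uniform 0.05, and a sample size for one of them.

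A second reply is that the error rate rises only if success on either outcome counts. This is correct, and the conclusion is conditional on it. With no rule stated, that reading remains open to whoever reports the trial.

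Several stronger readings are tempting but unsupported:

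- **Ten tests, with about 40% error if independent.** This counts the three Conners' subscales as primary. The article says only that the questions can be grouped that way.
- **Electrode-level testing, about 30 tests.** The article does not describe this as the plan.
- **A positive primary is likely by chance alone.** Even at 30%, a false positive is less likely than not. Theta power, alpha power and their ratios also share components, so independence is the least plausible case.
- **The stated 80% power is lost.** As written, nothing is adjusted, so the planned power for the Conners' Index is unchanged. Setting 80% against 67% also mixes a normal approximation with a t-test.
- **The ratio sites differ from those in the eligibility criteria and rationale.** The wording does differ, but this is a separate matter with no shown effect on the error rate.

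It is also fair to say that ranking the Conners' Index first reverses the protocol's emphasis on EEG, and that a late change of outcomes carries its own reporting risk. The fix allows for both.

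**Conclusion.** The point holds in limited form. Followed as written, and if any positive primary counts as success, the chance of at least one false-positive primary is about 7-10% with two tests, about 10-23% with five and about 11-30% with seven. These ranges assume equal correlations from 0.9 down to 0. The article supplies neither the correlations nor an exact test count, so no single figure can be given, but every case exceeds 5%. Separately, the 80% power statement covers the Conners' ADHD Index only, and the brain-wave primary has no power basis.

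**What to change.** 1. Make the Conners' ADHD Index, the variable that sized the trial, the primary outcome at two-sided 0.05.
2. Choose one EEG measure from those already listed in the Electroencephalography section and name it before unblinding. Test it second in a fixed sequence, at 0.05, only if the first is significant.
3. Report the other EEG measures and the Conners' subscales as secondary or exploratory, with estimates and confidence intervals.
4. State that the 80% power covers the Conners' Index only.

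If the sponsor prefers to keep both outcomes primary, use Holm across the Conners' Index and the one named EEG measure. Restate the Conners' power as about 67-71% at 22 evaluable per arm. That is the Bonferroni-level minimum, at the assumed standardized difference of 0.835-0.845 worked back from 25 per arm.

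**Cost.** Protocol and registry text change, with no extra participants. The fixed sequence leaves the full 0.05 for the Conners' Index, but an EEG result could not be claimed as confirmatory if the Conners' result is null. The article expected recruitment to finish on 30 August 2021 and was published on 22 October 2022. Any change made after recruitment should therefore be dated and documented as made before unblinding.

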**Fig. 1 Fig1:**
[figure not shown]
Flow chart of the study protocol

### Objectives

Primary objectives are as follows:Compare the status of brain waves between the 2 groups and within each group, before and after intervention.Compare the mean ADHD symptoms severity between the 2 groups and within each group, before and after intervention.

In addition, the following objectives are the secondary objectives of the study:Compare the mean serum hs-CRP between the 2 groups and within each group, before and after intervention.Compare the mean of serum MDA, between the 2 groups and within each group, before and after intervention.Compare the mean of serum NO, between the 2 groups and within each group, before and after intervention.

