### Participants

Participants will be 50 patients with ADHD. Patients will be recruited from Imam-Hossein psychological services center affiliated with Shahid Sadoughi University of Medical Sciences, Yazd, Iran. The inclusion criteria will be as follows: age 7–13 years, ADHD diagnosed by a psychiatrist, IQ higher than 80, theta brain waves higher than 7 Hz, beta brain waves lower than 13 Hz, increasing theta/beta power ratio in frontal, temporal and central electrode sites, resident of Yazd city, and informed consent signed by one of the patient’s parents. Exclusion criteria will be as follows: other psychotic diseases, taking any medication for ADHD during the past year, hormonal disorders including Addison's disease, Cushing syndrome, hyperparathyroidism, hypo- and hyperthyroidism, chronic diseases such as cancer, diabetes, stroke, kidney disease, liver disease, multiple sclerosis, fibromyalgia, and Parkinson’s disease, addiction of parents to alcohol/drugs at the time of the child’s birth, adherence to any specific diet in the past year, taking multivitamins or mineral supplements more than twice a month in the last 6 months, being on a special diet during the past year, and unwillingness to continue the study. We measured serum concentration of vitamin D before study. This study will be conducted among patients with ADHD who have vitamin D deficiency and vitamin D insufficiency.

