### ADHD diagnosis

According to the Diagnostic and Text Revision of Statistical Manual of Mental Disorders-Fifth Edition (DSM-V) [47, 48], the diagnosis of ADHD will be done by a psychiatrist. Based on the DSM-V criteria, a person who has at least six of the listed symptoms of inattention or symptoms of hyperactivity–impulsivity persisting for at least 6 months which are disruptive and inappropriate for the person’s developmental level is defined as a patient with ADHD [47, 48].

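### Both primary objectives put uncontrolled within-arm before/after tests on an equal footing with the placebo-controlled comparison, although such tests cannot isolate a vitamin D effect; regression to the mean is the main worry for brain waves

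*Protocol article*

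**What the plan says.** The Study design section describes a randomized, double-blind, placebo-controlled trial and states: "The primary outcomes of the present study are the status of brain waves and the severity of ADHD symptoms". The Objectives section then turns each outcome into a double comparison. For brain waves the aim is to "Compare the status of brain waves between the 2 groups and within each group, before and after intervention"; for symptoms it is to "Compare the mean ADHD symptoms severity between the 2 groups and within each group, before and after intervention". The three secondary objectives (hs-CRP, MDA, NO) follow the same pattern. Nothing ranks the between-group part above the within-group part.

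The Statistical analysis section gives the within-group part its own tests: a paired t-test for normal variables, and otherwise "Wilcoxon test will be used to compare the abnormal data within the groups". One threshold, P < 0.05, applies to every test. The same section also plans between-arm tests of end values and of change, and names ANCOVA for covariates.

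On selection, the Participants section requires "theta brain waves higher than 7 Hz, beta brain waves lower than 13 Hz, increasing theta/beta power ratio in frontal, temporal and central electrode sites". The Electroencephalography section lists relative theta power and the theta/beta ratio among the analysed variables. For symptoms, entry is by psychiatrist diagnosis, which needs "at least six of the listed symptoms of inattention or symptoms of hyperactivity–impulsivity persisting for at least 6 months". The outcome instrument is a different one: "For this trial, Conners’ parent rating scale (CPRS) [51] will be used".

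**The concern.** A before/after test in one arm makes no use of the control arm. It answers whether the arm changed, not whether vitamin D changed it. A significant fall in the vitamin D arm could come from vitamin D, from regression to the mean after selection on an abnormal value, from a placebo response in parents' ratings, from drift when the same parent repeats the scale, or from time. The placebo arm is there to remove the last four, and only the between-arm comparison does so.

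Because the within-arm comparison is part of each primary objective and is tested at the same threshold, a reader of the results could take part of a primary objective as answered by an uncontrolled change. A pattern of vitamin D significant and placebo not significant could also be read as a difference between arms, which it is not.

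The brain-wave objective is the most exposed to regression to the mean, because children enter on the same kind of measurement that is later tested.

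**Working it through.** **The plan's own figure.** The Sample size section gives 25 per group after about 10% drop-out, from n = 2S²(z_α/2 + z_β)²/(x1 − x2)². The means and SD are not printed, so 25 cannot be derived forward. Working back, 22 per group before drop-out gives 22/0.9 = 24.4, rounded up to 25, whereas 23 gives 25.6, rounded up to 26. The implied standardized difference is (1.96 + 0.84) × √(2/22) ≈ 0.85. What matters here is that this is a two-group formula: the trial was sized for the between-arm comparison.

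**Where selection touches an outcome.**
- Brain waves: entry requires "increasing theta/beta power ratio in frontal, temporal and central electrode sites". Theta power at frontal and central electrodes and the theta/beta ratio in motor cortices are outcomes. The overlap is close but not exact.
- Symptoms: entry is by diagnosis, with no minimum score on the Conners parent scale. Selection is indirect.
- NO, MDA, hs-CRP: no entry criterion selects on these measures.
- Serum vitamin D: low levels are required at entry, but it is not a listed primary or secondary outcome.

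**Size of the drift if selection is on the analysed baseline.** Inputs from the protocol: 25 per arm, two-sided 0.05, paired t-test. Assumptions not in the protocol: cut-off c in SD units, test-retest correlation r, no treatment effect, no time trend.

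For a standard normal baseline above c, the mean baseline is φ(c)/(1 − Φ(c)), which is 1.525 at c = 1. The expected fall is (1 − r) times that. At r = 0.7 it is 0.3 × 1.525 = 0.46 SD.

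The table gives the chance of significant improvement in one arm under no effect (20,000 simulated trials per cell, n = 25):

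| Cut-off | r = 0.5 | 0.6 | 0.7 | 0.8 | 0.9 |
|---|---|---|---|---|---|
| None | 2.6% | 2.5% | 2.5% | 2.6% | 2.4% |
| Upper half (c = 0) | 54.9% | 45.3% | 34.6% | 23.8% | 13.6% |
| c = 1 | 98.6% | 94.5% | 85.9% | 67.6% | 38.8% |
| c = 1.5 | about 100% | 99.5% | 96.9% | 86.8% | 57.0% |

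In the same simulated trials, the independent t-test of change between arms was significant in 4.7% to 5.4%, whatever the selection. With 22 per arm the pattern is the same: 12.5% to 49.1% at c = 0 and 34.5% to 97.1% at c = 1.

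**If the qualifying EEG is a separate recording.** With a stable true score and independent errors, the simulated mean drift was within 0.002 SD of zero for reliabilities of 0.6 to 0.9. The paired test then returns to about 0.05/2 = 2.5% in the direction of improvement.

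**One arm significant, the other not.** If both arms share the same true change and each within-arm test has power p, the chance that vitamin D is significant and placebo is not is p(1 − p): 0.2 × 0.8 = 16%, 0.5 × 0.5 = 25%, 0.8 × 0.2 = 16%. This needs no regression to the mean; any shared change will do.

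**The case against.** The strongest reply is that the controlled comparison is already planned. Each objective names the between-group comparison first, the analysis section tests change between arms and names ANCOVA, and the sample size formula is for two groups. No sentence says that a one-arm result establishes efficacy. All of this stands. A reader might infer that the trial's causal comparison is compromised, but it is not: randomization protects the between-arm test, whose error rate stays near 5%. The defect is that nothing makes that test decisive.

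A reader might also infer that regression to the mean is bound to produce false improvement. The protocol does not support that. It gives no cut-off for the theta/beta ratio and no test-retest reliability. The Electroencephalography section describes one EEG before the intervention, but no text says whether it is also the qualifying recording, and the schedule figure is not shown. The electrode sites for entry and outcome overlap only in part, so truncation on the analysed variable itself is the worst case.

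Nor does the regression argument carry over equally to every outcome. Symptoms are selected only through a diagnosis that requires persistence, the three serum markers are not selected on, and regression in vitamin D itself feeds no listed objective. For these, what remains is the general point that a one-arm test has no control.

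Finally, 2p(1 − p), or 32–50%, is the chance that exactly one arm is significant. It counts both directions; the misleading direction is half of it.

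**Conclusion.** The point holds in this form. Both primary objectives set an uncontrolled within-arm test at P < 0.05 beside the placebo-controlled comparison, with no ranking, and a within-arm test cannot attribute change to vitamin D. That conclusion rests on the text alone and needs no assumption.

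The size of the regression problem does depend on assumptions. For an outcome selected on its own analysed baseline, false improvement in one arm runs from about 14% to nearly 100% over the cut-offs and correlations examined. It falls to about 2.5% with no selection or with a separate qualifying EEG and independent errors. The protocol does not say where in this range the trial lies. The 16–25% chance of a misleading split between arms assumes a shared true change and within-arm power of 20–80%.

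This should be corrected, but it does not invalidate the planned between-arm analysis.

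**What to change.** - State that efficacy conclusions for the primary and secondary outcomes rest only on the between-arm comparison at week 8 adjusted for baseline, using the ANCOVA already named in the Statistical analysis section.
- Remove the within-group clause from both primary objectives.
- Report within-arm changes descriptively, and say that they are not evidence of efficacy.

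The cost is a wording change and the ethics committee approval that the Ethics and trial registration section requires for changes in objectives. No new data are needed. The Trial status section expected recruitment to end on 30 August 2021, so the change bears on analysis and reporting rather than on trial conduct.
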